#### Analysis of the primary endpoint

The primary endpoint 28-day mortality (dead at 28 days: yes or no) which will be analyzed using a logistic regression model adjusting the treatment effect for sex, pulmonary focus of infection (yes/no), baseline lactate (< 4.5/ ≥ 4.5 mmol/l), and center will be used. Superiority of the experimental intervention compared to the control intervention can be concluded if the upper boundary of the two-sided 95% confidence interval for the adjusted odds ratio (experimental intervention / control intervention) is below 1.

Patients will be followed up even after premature discontinuation of study intervention, and all collected data will be used in the primary analysis. Since patients enrolled in this study are critically ill, the rate of drop-out and loss to follow-up is expected to be very low. Nevertheless, if the vital status at day 28 is unknown for a patient, this patient will be considered dead at day 28 in the primary analysis.

As a sensitivity analysis, the missing vital status at day 28 will be handled using the multiple imputation.

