## Methods

### Study setting

A total of 274 septic shock patients (1:1 randomization) will be included in approximately 26 study centers. The study is planned at intensive care units (ICUs) of the following medical facilities in Germany, Switzerland, and Austria (EXCHANGE-2 study group):

In Germany: Hannover Medical School, Medical Intensive Care, Hannover Medical School, Anesthesiology Intensive Care, University Hospital Bonn (UKB), University Hospital Charite, Hospital St. Joseph, Berlin, Hospital Braunschweig, Reinkenheide Hospital, Bremerhaven, University Hospital Erlangen, University Hospital Essen, University Hospital Hamburg Eppendorf, Hospital Hannover Region, University Hospital Halle, University Hospital Heidelberg, University Hospital Jena, University Hospital Kiel Schleswig–Holstein (UKSH), Kiel, University Hospital Cologne, Hospital Cologne-Meerheim, Hospital Magdeburg, University Hospital Muenster Anesthesiology, University Hospital Rostock, Marienhospital Stuttgart, Stuttgart, Germany, University Hospital Munich (TU), University Hospital Munich (TU)**,** University Hospital Zurich (Switzerland), Inselspital Bern (Switzerland), Landeskrankenhaus Innsbruck (Austria) and “Allgemeines Krankenhaus der Stadt Wien,” Vienna (Austria).

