### Sample size

The primary aim of the study is to demonstrate superiority of SOC + TPE compared to SOC alone with regard to the primary endpoint 28-day mortality. In a prospective, monocentric, non-controlled pilot study of the TPE treatment in patients with septic shock, the observed 28-day mortality rate was 65%, while the predicted mortality rate using the APACHE-II-score was as high as 91% [10]. Meanwhile, two randomized clinical trials have been conducted. In one (small, *n* = 20 vs 20) randomized control trial, the observed mortality rate of the TPE-treated patients was 40% in contrast to 50% in the control group, resulting in a risk difference of − 10% with a 95% CI of [− 0,41;0,21] [14]. In another randomized control trial, the observed mortality rate of the treated patients was 33.3 and 53.8% in the control group, resulting in a risk difference of − 21% with a 95% CI of [− 0.39; − 0.02] [8]. For sample size calculation, we considered the two RCTs only and combined the outcome in a meta-analysis. The treatment procedures were similar, and the two trials are very homogeneous (I2 of 0%). The meta-analysis resulted in a risk difference of − 18% with a 95% CI of [− 0.34; − 0.02]. This risk difference was used in the sample size calculation. Sample size calculation was done for a two-group continuity corrected chi-square test (Query Advisor 8.7.1.0). To detect a reduction in 28-day mortality rate from 60 to 42% in the experimental group with a two-sided type I error rate of 5% and a power of 80%, at least 131 patients per group are required. Thus, the total sample size to detect the expected effect on the 28-day mortality is 262 patients. Stratification for sex, center, pulmonary focus of infection (yes/no), and lactate (< / ≥ 4.5 mmol/) at randomization is assumed to increase power of the statistical test. Considering a drop-out rate of 5%, a total of 274 patients will be assigned to the trial, i.e., recruited.

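### Entering about 26 centres as ordinary covariates in the primary logistic model gives a 95% CI that mildly under-covers and, when there is a real effect, an overstated odds ratio

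*Protocol article*

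**What the plan says.** Under Analysis of the primary endpoint, the protocol article names death by day 28, "which will be analyzed using a logistic regression model adjusting the treatment effect for sex, pulmonary focus of infection (yes/no"), and completes the covariate list with "baseline lactate (< 4.5/ ≥ 4.5 mmol/l), and center will be used". Superiority is concluded "if the upper boundary of the two-sided 95% confidence interval for the adjusted odds ratio (experimental intervention / control intervention) is below 1".

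Study setting gives the size: "A total of 274 septic shock patients (1:1 randomization) will be included in approximately 26 study centers".

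No random effect, conditional likelihood, penalisation or pooling of small centres is named. Under Analyses of secondary endpoints, the parallel linear model for mean SOFA lists centre among the independent variables, beside the binary factors. The plain reading of the primary model is therefore one indicator per centre, less a reference. The same section has 90-day mortality follow the primary analysis.

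**The concern.** Maximum-likelihood logistic regression is unreliable when many indicators are each estimated from few patients. The treatment log odds ratio is pushed away from zero, and the model-based standard error is smaller than the true sampling variability. Here there are about 10.5 patients per centre.

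Much depends on this one interval. No interim analysis is planned, and the key secondary endpoints are tested confirmatorily only if the primary analysis is significant. The adjusted odds ratio would also be the headline estimate of benefit. An interval that under-covers therefore loosens both the superiority claim and the gate behind it, and the reported effect would look somewhat larger than it is.

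**Working it through.** **Inputs from the article.** 274 patients, 1:1, about 26 centres (Study setting). Mortality 60% against 42%, two-sided 5%, power 80%, 131 per group (Sample size). Decision rule: upper 95% limit below 1.

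**The plan's own figure.** With p̄ = 0.51 and difference 0.18:
- Uncorrected n = [1.960·√(2·0.51·0.49) + 0.842·√(0.60·0.40 + 0.42·0.58)]² / 0.18² = 119.9, so 120.
- Continuity-corrected n = (119.9/4)·[1 + √(1 + 4/(119.9·0.18))]² = 130.8, so 131, as stated.

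That calculation is for an unadjusted chi-square test, so it says nothing about how the logistic model behaves.

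**Information per coefficient.**
- Deaths: 137·0.60 + 137·0.42 = 139.7. Survivors: 274 − 139.7 = 134.3.
- Coefficients: 1 treatment + 3 binary factors + 25 centres = 29, plus an intercept.
- 134.3/29 = 4.6 survivors per coefficient; 274/26 = 10.5 patients per centre.
- Planned OR = (0.42/0.58)/(0.60/0.40) = 0.483, log OR −0.728.

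**Simulation.** 6,000 trials per scenario, 274 patients, 26 centres, permuted blocks within centre × sex × focus × lactate. Assumptions not in the article: block lengths 2 and 4; equal or unequal centre sizes; between-centre SD 0 or 0.5 on the logit scale; log odds ratios 0.8 for lactate and 0.2 for pulmonary focus.

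True OR = 1, in % (two-sided error / false superiority):

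| Centre sizes, SD | Centre indicators | Conditional on centre | No centre term |
|---|---|---|---|
| equal, 0 | 6.38 / 3.30 | 4.95 / 2.65 | 5.25 / 2.75 |
| unequal, 0 | 6.02 / 2.65 | 5.05 / 2.28 | 5.02 / 2.25 |
| equal, 0.5 | 6.37 / 3.27 | 5.20 / 2.73 | 4.77 / 2.55 |
| unequal, 0.5 | 6.35 / 3.13 | 5.22 / 2.47 | 4.85 / 2.27 |

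With indicators the mean model SE is 0.272–0.282 against an empirical SD of 0.289–0.300, so it is 5–6% too small. The median OR is 0.992–1.005: no shift.

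True OR = 0.483 (median OR / coverage % / power %):

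| Centre sizes, SD | Centre indicators | Conditional on centre |
|---|---|---|
| equal, 0 | 0.437 / 92.5 / 83.8 | 0.474 / 94.9 / 81.6 |
| unequal, 0 | 0.451 / 93.0 / 82.9 | 0.480 / 94.9 / 81.1 |
| equal, 0.5 | 0.440 / 92.2 / 82.0 | 0.477 / 94.9 / 79.8 |
| unequal, 0.5 | 0.449 / 92.9 / 82.1 | 0.478 / 94.5 / 80.2 |

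Overstatement of the log OR: ln 0.451/−0.728 = 1.09 and ln 0.437/−0.728 = 1.14, so about 9–14%.

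**Random intercept.** Two further simulations cover it.
- 3,000–6,000 trials per scenario, between-centre SD 0–0.4, penalised quasi-likelihood: two-sided error 5.0–5.2% against 5.9–6.6% with indicators, log OR −0.73 to −0.74, and power 80–82% for both.
- 2,000 trials per scenario: OR 0.477 with coverage about 94–95%, against about 0.44 and 92% with indicators, at the same power.

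**The case against.** **The article never says fixed effect or indicator.** A condensed article may leave the handling of centre to the full protocol or SAP, and a random intercept, conditioning or pooling rule there would remove most of the problem. This stands as a condition on the finding. It does not dispose of it: the article states the confirmatory model and its decision rule, lists centre beside the binary factors, and that model followed as written misses its nominal properties.

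**The excess is small.** This also stands. On the one-directional rule it is about 0.2 to 0.8 points. The Monte Carlo SE is √(0.025·0.975/6000) = 0.2 points, so the lowest figure (2.65%) is within one SE of nominal. The other three, 3.13 to 3.30%, are about three to four SEs above it.

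**Too narrow is a relative statement.** The interval is too narrow for its own sampling variability. It is still wider than that of a model without centre (mean SE about 0.275 against 0.255).

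**Stronger inferences a reader might draw are not supported.**
- That intention-to-treat is breached because centres with only deaths or only survivors carry no information on treatment. The article's ITT definition says who is analysed and as what; a non-informative stratum does not violate it. Conditional logistic regression loses the same centres.
- That leaving out age and baseline SOFA is an error. The model matches the stratification factors, and any power gain from adding covariates rests on a prognostic strength the article does not give.

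**Conclusion.** The point holds at moderate severity. Read plainly, the primary model gives a two-sided type I error of about 6%, false superiority of about 2.6 to 3.3% against 2.5%, and coverage of 92 to 93% at the planned effect, where an odds ratio of 0.48 would be reported as about 0.44 to 0.45.

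It would be wrong to conclude that the trial's error control fails or that a null treatment would appear beneficial on average. Under the null the estimate is over-dispersed, not displaced; the exaggeration needs a real effect. Nor is adjusting for centre a mistake, since centre is a stratification factor.

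The result assumes centre indicators fitted by ordinary maximum likelihood. It also rests on assumed centre sizes, between-centre SD, covariate effects and block lengths; the direction was the same in every scenario tried.

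**What to change.** State in the analysis plan that the primary logistic model has treatment, sex, pulmonary focus and lactate as fixed effects and centre as a random intercept. Name the estimation method and a fallback if the model does not converge, for example no centre term: in the simulation that model had a type I error of 4.8–5.3% and coverage of 94.4–94.9% at OR 0.483. Use the same handling for 90-day mortality. The linear models for SOFA and organ support-free days do not share this bias and can stay.

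Conditional logistic regression by centre is an alternative. It also restores nominal error, but it drops single-outcome centres, and its power was about 2 points below the inflated indicator model.

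The cost is a few sentences, with no change to sample size or data collection. Trial status reports that no patient had yet been recruited.

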#### Analyses of secondary endpoints

Analyses of the key secondary endpoints will be performed as follows:(i)The mean SOFA score will be analyzed as degree of organ failure measured by the per-patient mean daily SOFA score over 7 days. In case a patient dies before day 7, the daily SOFA score will be registered as 24 points for the following days until day 7. A linear regression model will be used for comparing the treatment arms, which includes mean daily SOFA score over 7 days as dependent variable, and treatment group, sex, pulmonary focus of infection (yes/no), baseline lactate (< 4.5/ ≥ 4.5 mmol/l), and center as independent variables. Superiority of the experimental intervention compared to the control intervention can be concluded if the upper boundary of the two-sided 95% confidence interval for the adjusted mean difference (experimental intervention minus control intervention) is below 0.A sensitivity analysis for the SOFA score will be performed using an exact test based on trimmed means [15]. This method follows the ITT principle in taking all randomized patients into account in the analysis without hypothesizing SOFA values for patients who die before day 7.(ii)Organ support-free days until day 28, determined as total days without need for invasive ventilation, vasopressor/inotropes, and RRT until day 28, will be analyzed similarly with a linear regression model with stratification factors of the randomization as co-variates. In case a patient dies before day 28, each remaining day until day 28 will be counted as a day with organ failure.

The confirmatory assessment of key secondary endpoints will be done in the above specified order as soon as the primary analysis of the primary endpoint is significant.

Other secondary endpoints:

The 90-day mortality (dead at day 90: yes or no) will be analyzed in line with the primary analysis of 28-day mortality. In addition, 28-/90-day mortality will be analyzed as time-to-event endpoint. The survival curves until day 28/90 will be estimated using the Kaplan–Meier method and compared using the log-rank test. Additionally, a Cox regression model will be utilized to estimate the hazard ratio between the treatment arms.

Other secondary endpoints (e.g., ICU length of stay, hospital length of stay, hemodynamics, arterial blood gas analysis) will be summarized by treatment group and compared with appropriate statistical tests.

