### Eligibility criteria

Patients have to fulfill all of the following inclusion criteria to be eligible for participation in the study:Onset of septic shock within < 24 h (SEPSIS-3 definition) ANDNorepinephrine (NE) dose of ≥ 0.4 μg/kg/min ≥ 30 min OR≥ 0.3 μg/kg/min + vasopressin (any dose)for ≥ 30 min (target mean arterial pressure (MAP) ≥ 65 mmHg) despite adequatecrystalloid fluid resuscitation of ≥ 30 ml/kg body weight ANDEstablished vascular access suitable for plasma exchange independent of study inclusion (due to established indication of renal replacement therapy (RRT), expected need for RRT within the next 48 h or other medical reasons as assessed by treating physician team)

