### Who will take informed consent

A stratified randomization approach will be used. Patients who meet the respective inclusion criteria and who or whose proxy or legal representative give written informed consent to participate will be included. If the legal representative is not available to give written consent at place, a telephone-based education of the legal representative will be performed and a consultant physician (not involved in the patient’s care) will sign the consent form on behalf. The written consent of the legal representative will then be obtained in retrospect as soon as possible. Once a patient meets the criteria of early (< 24 h) and severe septic shock (NE dose ≥ 0.4 μg/kg/min or NE dose of ≥ 0.3 μg/kg/min + vasopressin), the patient will be randomized. Permuted block randomization with variable block length and stratified by center, sex (m/f), pulmonary focus of infection (yes/no), and baseline (at screening) lactate (< 4.5/ ≥ 4.5 mmol/l) will be used to allocate patients to the intervention and the control groups in a 1:1 ratio. Randomization will be conducted centrally using a web-based approach (eCFR).

The investigator is responsible for obtaining patient’s/legal representative’s written informed consent after adequate explanation of the aim, study assessments, potential risks and benefits, and consequences of the study as well as alternative treatment options. If patients are incapable of giving consent due to unconsciousness, informed consent may be given by a legal representative who has been designated by the local court. After retrieval of capacity for informed consent, patients have to be informed about study-specific interventions that have already been done and about the treatments that are planned in the future.

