### Outcomes

#### Primary endpoint

The primary endpoint is 28-day mortality (Table 1).

**Table 1 Tab1:** Endpoints

PRIMARY Endpoint	28-day mortality
KEY SECONDARY Endpoint	
Extent of organ failure	indicated by: Mean Sequential Organ Failure Assessment (SOFA) score over the first 7 days following randomization and Organ support-free days (total days free of invasive ventilation, vasopressors/inotrops and RRT) until d28
(Further) SECONDARY Endpoints	
90-day mortality	
1-year mortality	
Length of stay (LOS)	Intensive Care Unit (ICU) LOS [days] Hospital LOS [days]
Basic hemodynamics 0 and 12 h, d1–7	Days free of vasopressor until day 28 [days] Norepinephrine dose [µg/kg/min] Dobutamine dose [µg/kg/min] Epinephrine dose [µg/kg/min] Vasopressin dose [U/kg/min] Vasoactive inotropic score (VIS) Mean arterial pressure (MAP) [mmHg] Heart rate (HR) [bpm] Central venous pressure (CVP) [mmHg] Central venous saturation (ScvO_2_) [%]
Extended hemodynamics 0 and 12 h, d1–7	Cardiac index (CI) [l/min/m^2^] Stroke volume variance (SVV) [%] Systemic vascular resistance index (SVRI) [dyn*s*cm-5*m^2^] Global end diastolic volume index (GEDI) [ml/m^2^] Extravascular lung water index (ELWI) [ml/kg] Pulmonary vascular permeability index (PVPI)
Arterial blood gas analysis (BGA) 0 and 12 h, d1–7	pH PCO_2_ [mmHg] HCO_3_^−^ [mmol/L] PO_2_ [mmHg] Lactate [mmol/L]
Respiratory function 0 and 12 h, d1–7	Days free of ventilator until day 28 [days] PO_2_/FiO_2_ ratio (PF ratio) Tidal volume (VT) [ml] Positive end-expiratory pressure (PEEP) [cmH_2_O] Peak pressure (Ppeak) [cmH_2_O] Plateau pressure (Pplat) [cmH_2_O] Respiratory Rate (RR) [1/min] Inspiratory Time (Tinsp) [s] Inspiratory Flow [l/min] End tidal CO_2_ (etCO_2_) [mmHg]
Renal function 0 and 12 h, d1–7, ICU discharge	Days free of renal replacement therapy (RRT) until day 28 [days] Presence of acute kidney injury (AKI) (KDIGO) [yes/no], 0 and 12 h, d1–7, ICU discharge AKI stage (KDIGO) [Stage 1 to 3], 0 and 12 h, d1–7, ICU discharge Need for RRT [yes/no], 0 and 12 h, d1–7, ICU discharge Estimated Creatinine-based Glomerular Filtration Rate (eGFR) (CKD-EPI) [ml/min], 0 and 12 h, d1–7, ICU discharge Fluid intake [ml/d], d1–7 Urine output [ml/d], d1–7 Ultrafiltration [ml/d], d1–7 Net daily fluid balance [ml/d], d1–7

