#### Key secondary endpoint

The key secondary endpoint is the extent of organ failure (Table 1) indicated by both:The mean Sequential Organ Failure Assessment (SOFA) score over the first 7 days following randomization with day 1 (d1) indicating the day of study inclusion (i.e., the day of the intervention). The SOFA score [13] will be recorded daily at inclusion and following the next 7 days.Organ support-free days (total days free of invasive ventilation, vasopressors / inotrops and RRT) until day 28.

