#### Subgroup analyses

Subgroup analyses will be performed for the primary and key secondary endpoints in the relevant subgroups including sex, age (≥ 60/ < 60), pulmonary focus of infection (yes/no), RRT (yes/no), pre-existing congestive heart failure NYHA III/IV (yes/no), pathogen (gram + /gram −), baseline lactate concentration (< 4.5/ ≥ 4.5 mmol/l).

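### The confirmatory model for organ support-free days leaves out RRT and invasive ventilation at randomization, and so probably gives up a little precision that could be had almost for free

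*Protocol article*

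**What the plan says.** The endpoint is defined under Key secondary endpoint as "Organ support-free days (total days free of invasive ventilation, vasopressors / inotrops and RRT) until day 28". Under Analyses of secondary endpoints, item (ii), it "will be analyzed similarly with a linear regression model with stratification factors of the randomization as co-variates". After a death, every remaining day up to day 28 counts as a day with organ failure.

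The covariates are therefore the randomization factors, which the article gives as "stratified by center, sex (m/f), pulmonary focus of infection (yes/no), and baseline (at screening) lactate (< 4.5/ ≥ 4.5 mmol/l". Item (i), mean SOFA, names the same four.

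The endpoint has confirmatory status: "The confirmatory assessment of key secondary endpoints will be done in the above specified order", once the primary endpoint is significant. Mean SOFA comes first and organ support-free days second.

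On baseline support, Table 1 (renal function) lists "Need for RRT [yes/no], 0 and 12 h, d1–7, ICU discharge". Its respiratory row lists tidal volume, PEEP, peak pressure and plateau pressure at 0 h. Eligibility criteria require vascular access suitable for plasma exchange, placed for an established RRT indication, or "expected need for RRT within the next 48 h or other medical reasons as assessed by treating physician team". Subgroup analyses names "pulmonary focus of infection (yes/no), RRT (yes/no" among the factors for the primary and key secondary endpoints.

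**The concern.** The outcome counts days free of three supports. All patients are on norepinephrine at entry, so at randomization they can differ only in the other two. RRT status can vary by design, because the access criterion admits patients already on RRT, patients expected to need it, and patients with access for other reasons. A patient already ventilated and on RRT at 0 h plausibly has fewer support-free days ahead than one on vasopressors alone.

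Neither status is a stratification factor or a covariate. Pulmonary focus is at best a loose stand-in for ventilation, and none of the four factors stands in for RRT. The article treats RRT as relevant enough to this endpoint to define a subgroup, yet leaves it out of the main model without giving a reason.

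At stake is the width of the confidence interval for a confirmatory endpoint, and how far a chance imbalance in baseline support can move the estimate in the one trial that is run.

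**Working it through.** **1. The plan's own figure.** The article sizes the trial only for 28-day mortality: 60% vs 42%, two-sided 5%, 80% power, continuity-corrected chi-square. Recomputing gives 131 per arm, as stated (120 without the correction). With 5% drop-out, 262 / 0.95 = 275.8, or 276 against the stated 274, a difference of 2 patients. No power, standard deviation or effect is given for organ support-free days, so everything below rests on assumptions.

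**2. Effect of adding the covariates.** In a linear model for a randomized trial, adding baseline covariates leaves the target (the mean difference) unchanged and multiplies its standard error by about sqrt(1 − R²). Here R² is the partial R-squared of the two variables, given what is already in the model. For a reference power of 80% without them, the expected test statistic is 1.960 + 0.8416 = 2.8016. With 137 per arm this is a difference of 2.8016 × sqrt(2/137) = 0.339 standard deviations. Then

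power = Φ(2.8016 / sqrt(1 − R²) − 1.96), and equivalent sample size = 274 / (1 − R²).

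| Partial R² | SE multiplied by | Power | Equivalent N |
|---|---|---|---|
| 0 | 1.000 | 80.0% | 274 |
| 0.02 | 0.990 | 80.8% | 280 |
| 0.05 | 0.975 | 82.0% | 288 |
| 0.10 | 0.949 | 84.0% | 304 |
| 0.15 | 0.922 | 86.0% | 322 |

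**3. Which R² is plausible.** The endpoint was simulated with overall mortality (60 + 42) / 2 = 51% and 0 days for deaths, which simplifies the article's rule. Survivors had 28 days minus a gamma-distributed support duration. Ventilation prevalence was 60%, 75% or 90%, and RRT prevalence 30%, 50% or 80%. Each baseline support raised the log-odds of death and lengthened mean support:

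| Assumed strength, per support | R² | SE falls by | 80% power becomes |
|---|---|---|---|
| Weak (log-odds 0.2, +2 days) | 0.009–0.015 | 0.4–0.8% | 80.3–80.6% |
| Moderate (0.5, +4 days) | 0.037–0.069 | 1.8–3.5% | 81.4–82.7% |
| Strong (1.0, +6 days) | 0.094–0.174 | 4.8–9.1% | 83.7–86.9% |

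This simulation held no other covariates. To the extent that the stratification factors already carry some of the same information, the partial R² in the planned model would be somewhat smaller.

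**4. A second form of the simulation.** This one used log-normal durations, 274 patients, 60% vs 42% mortality and 600 trials per setting, with and without pulmonary focus and lactate as covariates. An odds ratio for death and a lengthening factor of 1.2 each lowered the residual variance by about 1%, and power changed by −1 to +1 point, which is noise. At 1.5 each, variance fell 4–6% and power rose 1–3 points. At 2 each, variance fell 13–16% and power rose 3–7 points. At 2.5 each, variance fell 21–24% and power rose 3–8 points. The direction is the same once the effects are moderate.

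**5. Cost.** The planned model spends about 1 (intercept) + 1 (treatment) + 3 (sex, focus, lactate) + 25 (26 centers) = 30 parameters. That leaves 274 − 30 = 244 residual degrees of freedom, and 242 after adding two.

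**The case against.** The planned model is coherent and standard: it adjusts for every stratification factor and uses the same set as the primary endpoint and mean SOFA. It contains no contradiction, and adding further prognostic covariates is optional. The endpoint is reached only if 28-day mortality and then mean SOFA are significant, and the trial was not sized for it. The RRT subgroup analysis will in any case show results by RRT status.

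The contrast may also be narrow. Most entry routes involve current or expected RRT, so patients not on RRT at 0 h will include some about to start. About half of the patients are expected to die and lose their remaining days; mortality therefore drives much of the spread, and these two variables predict it only in part. The article shows no explicit yes/no item for ventilation at 0 h, and the schedule in Table 2 is not reproduced.

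Most of this stands and limits the size. It does not show any harm from adding the covariates. A uniform covariate set is tidy but buys no validity, and subgroup results do not restore precision in the main comparison. The model is stated in the article rather than left open, so commenting on it is fair.

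A reader might infer that leaving out these variables biases the comparison or invalidates the test. It does neither: randomization protects both, and a chance imbalance adds variance, not bias. A reader might also take RRT and ventilation status as the baseline value of the outcome and expect them to explain a large share of it, for instance an R-squared of 0.25 and 90% power. The article gives no figure to support that. Nobody is support-free at entry, so these are prognostic factors and not a baseline measurement of the endpoint.

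**Conclusion.** The point holds as a minor matter of efficiency. The analysis of organ support-free days is valid and unbiased as written, but it leaves out two likely prognostic variables that are available, or derivable, at randomization. The likely gain from including them is about 0 to 3 points on a reference power of 80% if they are weakly to moderately prognostic, and up to about 7 points (R-squared 0.17) under strong assumptions. The prevalences, prognostic effects and reference power are all assumed, because the article gives none of them for this endpoint. The direction is firm whenever the variables are prognostic; the size is not.

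**What to change.** In Analyses of secondary endpoints, item (ii), and in the SAP, prespecify RRT (yes/no) and invasive ventilation (yes/no) at randomization as covariates, in addition to the stratification factors. Do this before any unblinded data are seen, since covariates chosen afterwards would not carry the same confirmatory weight. State how ventilation status is derived from the 0 h respiratory data, or confirm that the eCRF holds a yes/no item. Because treatment is open-label, fix both values as those at randomization, not after allocation is known.

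The cost is 2 degrees of freedom and a line or two of text. No patients or procedures are added, and no new data collection is needed as long as ventilation status can be derived as described.

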### Assignment of interventions: allocation

Permuted block randomization with variable block length stratified by sex, center, pulmonary focus of infection (yes/no), and lactate (< / ≥ 4.5 mmol/) at randomization will be used to allocate patients to both study arms. Only the statistician and the unblinded data manager will have access to the randomization list. The allocation is performed via the eCRF system. Only after the patient has been documented with in- and exclusion criteria in the eCRF by the study site, the allocation of the patient to a treatment group will be displayed in the eCRF automatically according to the sequence determined by the randomization list. For the study sites, it is not possible to see the randomization list.

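### The log-rank test for 28-/90-day survival names no strata and the Cox model no covariates, although randomisation is stratified and the other main models adjust for the factors

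*Protocol article*

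**What the plan says.** Allocation is described twice in the protocol article, with the same four factors. The section on informed consent has it "stratified by center, sex (m/f), pulmonary focus of infection (yes/no") and by baseline lactate below or at least 4.5 mmol/l. The allocation section repeats this: "Permuted block randomization with variable block length stratified by sex, center, pulmonary focus of infection", and lactate. The sample size section adds that stratification is expected to raise the power of the test, without giving a figure.

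The analyses then use these factors:

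- Primary endpoint: a "logistic regression model adjusting the treatment effect for sex, pulmonary focus of infection (yes/no), baseline lactate" and center.
- Mean SOFA score: a linear model with the same four factors.
- Organ support-free days: a linear model with the stratification factors as covariates.
- 90-day mortality as a yes/no outcome: analysed in the same way as the primary endpoint.

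In addition, 28- and 90-day mortality are treated as time-to-event outcomes under the other secondary endpoints. Kaplan-Meier curves are "compared using the log-rank test". The next sentence reads: "Additionally, a Cox regression model will be utilized to estimate the hazard ratio between the treatment arms". Neither sentence mentions strata or covariates.

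**The concern.** Stratified allocation makes the arms more alike on the stratification factors than simple randomisation would. If those factors predict death, the treatment comparison varies less from trial to trial than the variance of a plain log-rank test assumes. The test then rejects less often than its nominal 5% under no effect, and loses some power under a real one. A Cox model with treatment alone has a related feature: leaving out prognostic covariates pulls its hazard ratio toward 1 compared with the effect conditional on them.

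The article avoids this in its other main mortality and organ-failure models, so the survival analyses stand apart from its own convention. What is at stake is presentational and modest. Readers will see survival curves with a log-rank p-value beside an adjusted primary result. If the two fall on opposite sides of 0.05, the difference in adjustment could be part of the reason. Choosing a stratified or adjusted version only after seeing the data would look selective.

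**Working it through.** **1. The plan's own figure.** The sample size section assumes 28-day mortality of 60% under control and 42% under TPE, for a continuity-corrected chi-square test. Its result reads: "with a two-sided type I error rate of 5% and a power of 80%, at least 131 patients per group are required". With mean rate 0.51 and difference 0.18:

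n0 = [1.96·√(2·0.51·0.49) + 0.8416·√(0.60·0.40 + 0.42·0.58)]² / 0.18² = (1.386 + 0.585)² / 0.0324 ≈ 119.9, so 120 without the correction.

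n = (n0/4)·[1 + √(1 + 4/(n0·0.18))]² = (119.9/4)·(1 + 1.0887)² ≈ 130.8, so 131 per group. The stated figure is reproduced. The article gives no figure for the log-rank or Cox analysis.

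**2. The same effect as a hazard ratio.** Under proportional hazards, HR = ln(1 − 0.42)/ln(1 − 0.60) = ln 0.58/ln 0.40 = 0.594. With 137 patients per arm, expected deaths by day 28 are 137 × (0.60 + 0.42) ≈ 140. Without any heterogeneity, log-rank power = Φ(√(140/4)·|ln 0.594| − 1.96) ≈ 87%.

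**3. How fine the stratification is.** Study setting: "A total of 274 septic shock patients (1:1 randomization) will be included in approximately 26 study centers". Three two-level factors give 8 cells per center, so 26 × 8 = 208 cells, and 274/208 ≈ 1.3 patients per cell. Most blocks stay unfilled. This weakens the balance that stratification achieves, and therefore limits how conservative a plain test becomes. A simulation has to include center in the allocation to show this.

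**4. Simulation.** The setting was 274 patients, 26 centers of unequal size, permuted blocks within center × 8 cells, exponential survival censored at day 28, conditional HR 1 or 0.594, and 3,000 trials per setting. Monte Carlo standard error is about 0.4 points for type I error and 0.7-0.9 for power. The documents give no prognostic strengths, factor frequencies or block lengths, so all are assumptions. Block lengths were 2/4 or 4/6, and ranges below span the two. Factor frequencies were 35% for one sex, 45% pulmonary focus and 50% high lactate.

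Three analyses were compared:

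- plain log-rank: Z = Σ(O − E)/√ΣV
- log-rank stratified by the 8 sex × focus × lactate cells, with O − E and V summed over cells
- Cox model with treatment, sex, focus and lactate

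Neither of the last two includes center.

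| Assumed HR for lactate / focus / sex; SD of center log-hazards | Type I error, plain | Type I error, stratified | Power, plain | Power, stratified | Power, adjusted Cox | Mean HR, unadjusted vs adjusted |
|---|---|---|---|---|---|---|
| Moderate: 1.6 / 1.2 / 1.1; 0.3 | 3.8-4.6% | 4.3-4.9% | 83.4-83.7% | 83.8-84.1% | 85.0-85.3% | 0.61 vs 0.60 |
| Strong: 2.5 / 1.5 / 1.2; 0.5 | 3.7-4.1% | 4.4-5.2% | 76.4-77.4% | 80.0-80.6% | 81.7-81.8% | 0.64 vs 0.62 |

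The baseline hazard was not recalibrated between rows, so only comparisons within a row are meaningful.

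**5. Differences within a row, by block setting.** Moderate: the plain test is 0.4-0.5 points below the stratified test and 1.6 points below the adjusted Cox model. Strong: it is 3.2-3.6 points below the stratified test and 4.3-5.3 points below the adjusted Cox model.

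An extreme setting (4 / 2 / 1.5; SD 0.7) gave type I error of 2.1-3.3% for the plain test and power of 64%, against 75-76% stratified. Nothing in the article suggests factors that strong.

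**The case against.** The best counter-argument is that this is a condensed article, and strata or covariates for a supportive analysis are details commonly left to the full protocol or analysis plan. For the Cox model this largely stands. A reader might infer that the model ignores the randomisation factors, but the sentence neither names nor excludes covariates. The most that can be said is that it is silent. For the log-rank test the argument is weaker. The article states its adjustment for the primary, key secondary and binary 90-day analyses, and then names a test whose ordinary meaning is unstratified.

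A second argument is that the plain log-rank test is legitimate: it controls the type I error and matches the marginal curves it accompanies. That is correct, so the point concerns efficiency and consistency, not validity.

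Two stronger readings are tempting and should be set aside:

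- That the 90-day survival comparison rests on these tests. It does not. Binary 90-day mortality has the adjusted logistic analysis, and the time-to-event analyses come on top of it.
- That the missing adjustment is what makes the hazard ratio not comparable with the primary odds ratio. The two are different measures and would differ numerically even with identical covariates. What is lost is only a matching adjustment set.

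**Conclusion.** The point holds as a minor improvement. As written, the log-rank test is unstratified and the Cox sentence leaves its covariates open, out of line with the randomisation and with the article's other main models. The plain test is valid and errs on the conservative side. The power loss is about 0.5 to 1.6 points with moderate factors and about 3 to 5 points with strong ones, and an unadjusted hazard ratio shifts by 0.01 to 0.02.

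These sizes rest on assumed prognostic strengths, factor frequencies, block lengths and exponential survival, and were computed for day 28 only. With moderate factors the shortfall in type I error is close to simulation error. It would therefore be wrong to state flatly that the p-values will be too large: with weakly prognostic factors the effect would be negligible.

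A reader might also infer a threat to the trial's main claim. The documents do not support that. The confirmatory sequence contains the primary endpoint and the two key secondary endpoints, all adjusted. The survival analyses lie outside it, and no false-positive risk is created.

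**What to change.** In the section on analyses of secondary endpoints, state that the log-rank test is stratified by sex, pulmonary focus and lactate category, and that the Cox model includes treatment and the randomisation factors, with center handled as in the primary model. Keep the Kaplan-Meier curves as the display.

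Center is left out of the log-rank strata on purpose. Adding it would give about 208 strata for 274 patients, many holding one patient or only one arm and so contributing nothing. The two survival analyses will then differ in their use of center, and the text should say so. The simulated Cox model had no center term, so the power figures above do not describe the Cox model proposed here exactly.

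The cost is one sentence, fixed before the data are seen. All the factors are already recorded for randomisation, and there is no added burden for patients or sites.
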